# Guided meditation for vision acuity training on adolescent myopia: study protocol for an open-label, prospective, multicenter, randomized controlled trial

**DOI:** 10.1186/s13063-021-05922-1

**Published:** 2022-01-06

**Keywords:** Simple myopia, Meditation, Vision acuity training, Randomized controlled trial

## Abstract

**Background:**

Currently, the population with myopia climbs steadily, and is developing toward younger age, posing a great concern to the health of adolescents. Myopia in severe cases can cause irreversible consequences such as glaucoma, blindness, and other complications. At present, the solutions for myopia are glasses, medication, and surgery. This study aims to investigate the role of a physiotherapy category based on guided meditation for vision acuity training on adolescent myopia.

**Methods:**

This is a prospective, randomized, multicenter clinical trial. One thousand one hundred forty primary and secondary school students aged 8–18 years old from 27 schools will be recruited and randomly divided into an experimental and a control group at a ratio of 2:1 in two phases, with a training period of 30 days in each phase and a follow-up period of 3 months. No interventions will be conducted during the follow-up period, nor will other interventions employed. Inclusion criteria will meet the diagnostic criteria for simple myopia and −6.00D ≤ spherical lenses ≤ −0.50D and cylindrical lenses ≤1.50D. The primary observation index will be to compare the statistical differences in distant visual acuity between the two groups; the secondary observation indexes will be ocular symptoms (mainly including eye fatigue, dryness, pain, double vision, neck pain, thought disorders, and lags in response), diopter, and astigmatism.

**Discussion:**

The purpose of this two-phase trial is to compare the clinical effectiveness of focused vision-guided meditation with Chinese eye exercises that are also non-pharmacological, non-invasive interventions for myopia, and to maximize the benefit to the subjects. The results will indicate whether the training based on focused vision-guided meditation has the ability to improve distant visual acuity, relieve ocular symptoms, and ameliorate diopter. In addition, this trial will provide clinical efficacy of the training, which is expected to provide meaningful data for vision rehabilitation. At the same time, the vision acuity training method, which is permeated with the concept of Traditional Chinese Medicine (TCM) rehabilitation and health maintenance, will be applied to achieve the goal of preventing or alleviating myopic development and reducing myopia rate.

**Trial registration:**

Chinese Clinical Trial Registry ChiCTR2000038642. Registered on 26 September 2020

## Background

Myopia, also known as short-sightedness or near-sightedness, is a common vision condition in which you can see objects clearly when near to your eye, but obscure when farther away. It occurs when your eyeball is unable to focus precisely, forming images in front instead of right on your retina, resulting in a blurry appearance for distant objects. It is a very common condition that typically starts in childhood. And certain risk factors may increase the likelihood of developing nearsightedness, such as genetics and environmental conditions.

The prevalence of myopia is increasing yearly and has become one of the most serious public health problems worldwide [1]. It is expected that by 2050, 50% of the world’s population will be affected by myopia [2]. The increase in the myopic population is accompanied by an earlier age of onset, usually occurring between 6 and 8 years old, growing rapidly between 13 and 16 years of age, and stabilizing after 16 years old [3]. In countries of East and Southeast Asia, approximately 80 to 90% of urban adolescents have myopia by the time they graduate from high school [1], and China has the second highest number of adolescents with myopia in the world with more than 450 million [4].

Myopia can be divided into simple myopia and pathological myopia. The most common one in adolescents is the simple myopia, which is induced by a combination of genetic and environmental factors, and is related to the weakening of visual regulation caused by spasm of the extraocular and ciliary muscles, which will gradually lead to the growth of the eye axis if it is not restored in time. Therefore, the functions of the extraocular and ciliary muscles are crucial for maintaining good vision [5]. If not corrected in time, myopia will lead to serious and irreversible complications such as retinal detachment, macular degeneration, glaucoma, and blindness [6]. Strengthening vision protection for adolescents has become an urgent issue that needs to be addressed.

Currently, optical correction by glasses is the main intervention method for simple myopia, but it cannot improve the visual acuity of the naked eye. Drugs such as atropine can improve visual acuity, but once the drug is discontinued, the vision problem will rebound or cause even worsen myopia, along with some side effects such as photophobia, blurred vision, and allergic conjunctivitis [7]. Laser surgery may be complicated by other eye diseases, such as near vision impairment and dry eye, and has age restrictions [8, 9].

Vision acuity training refers to the use of optical, psychological, physical, and other methods to produce a certain cognitive load on the visual system of the eyes (including regulation, convergence, eye movements, and the associated movements between them), in a bid to improve the visual function and visual comfort of the visual system and achieve the goal of improving and repairing visual abnormalities in both eyes. It is considered as a purely physical, non-invasive, non-drug therapy with no side effects to relieve eye fatigue and improve vision, with a long history. The earliest and most widely known is the Bates Vision Acuity Training Method, including eye sunbathing, palm massage, rope games, ruler games, pencil games, etc. But due to the complexity of its training, long cycles, etc., it has not been widely promoted. At present, the common vision training mainly relieves the ciliary muscle tension by repeatedly focusing on the distant visual target, looking at the distance and movement of the image to adjust the function of the extraocular muscles, and through the different light color changes to stimulate the visual cortex, as ways to improve vision and restore to a good visual system.

Defined as a form of training to improve concentration and mood, meditation involves a range of practices such as mindfulness meditation, yoga, tai chi, and qigong [10]. Meditation is however not limited to sitting still; one can be in a meditative state while walking, standing, sitting, lying, or even working [11]. A recent article in the *New England Journal of Medicine* highly valued the contemporary value of meditation as “embarking on a new era in psychosomatic medicine” [12]. In recent years, meditation has attracted widespread attention and in-depth research across the world, mainly focusing on psychological diseases [13, 14], pain [15], sleep disorders [16], chronic disease rehabilitation [17, 18], and other fields. However, due to the long intervention period, complex indicators, and difficulty in objective quantification, it is difficult to fully reflect the effects of meditation.

The training based on guided meditation for vision acuity belongs to a kind of regulation training method in the scope of physiotherapy, which mainly uses audio and video guidance to instruct myopia patients to focus on breathing, associate images, enter a meditation-like state, and specialize the current practice. Meanwhile, the patients could exercise the extraocular and ciliary muscles by incorporating simple actions such as hand-eye coordination with the stimulation of meridian points. In doing so, visual function and comfort can be improved. As this training method is simple and has a short period, it is welcomed by youngsters, and the indicators for evaluating vision acuity are simple, so it is easy to quantify the effect objectively.

Therefore, we will conduct a multicenter, randomized controlled study based on guided meditation for vision training. It is hoped that this study, from the perspective of psychosomatic medicine, can stimulate the self-healing ability in adolescent students under the guidance of external physical operations.

## Methods/design

### Ethics

This trial is designed in accordance with the “Ethical Review of Biomedical Research Involving Human Subjects” issued by the Ministry of Health of the People’s Republic of China. The implementation of this project has been reviewed and approved by the Ethical Review Committee of Beijing University of Chinese Medicine (BUCM) for [name] (4 June 2020, approval number: 2020 BZYLL0306); [name], the vice president of BUCM, is the authorized representative under subtitle ethics approval and consent (Ethical Approval Document-Chinese version and Ethical Approval Document-English version). Written informed consent will be obtained from each subject and his/her guardians.

### Study design

This study will be a prospective, multicenter, randomized controlled clinical trial. The included subjects (*n* = 1140) will be randomly assigned to the experimental (*n* = 760) and control (*n* = 380) groups in a 2:1 ratio. The aim of this study is to objectively evaluate the clinical efficacy of the guided meditation of vision training for adolescent myopia. This report will be compiled according to the SPIRIT (Standard Protocol Items: Recommendations for Interventional Trials) 2013 Statement “Defining Standard Protocol Items for Clinical Trials” (Fig. 1 and Table 1).

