#### Second phase

After the completion of the first phase of the randomized controlled study, data will be collected and compared between the vision acuity training group and the Chinese eye exercise group.

The second phase will be carried out based on the experimental results of the first phase. If the first phase showed that the visual training effect was not significantly better than eye exercises, the trial was terminated. If the data proved that the effect of the meditation group was not superior to the control group, and the results were statistically significant, the second phase of the experiment will be carried out.

Since the purpose of this study is to improve the naked eye visual acuity that affects life and work, the experimental group has achieved this effect in the first stage. In order to ensure the maximum benefit of the subjects, only the control group and the experimental group of the first stage were given the same treatment plan in the second stage, namely guided meditation for vision acuity training. The results of phase 2 subjects (the control group at phase 1) were compared with the results of eye exercises at phase 1.

The subjects in this study are adolescent students with simple myopia and no other comorbidities of chronic diseases. If the subjects need to combine medication due to cold or other reasons, they should be recorded promptly.

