## Statistical analysis

### Sample size

The sample size will be estimated based on our early observations [23]. The treatment group was 4.98 ± 0.14, and the control group was 4.92 ± 0.24. Under 20% dropout rate, with the two-tailed *α* = 0.05 and *β* = 0.1 (test efficacy of 0.9), experimental group: control group = 2:1, PASS 15.0 software calculation shows 380 in the experimental group and 190 in the control group. Due to the possible center effect, the final sample size is suggested to be twice expanded. Thus, it is finally confirmed there will be 1140 cases in total, with 760 cases in the experimental group and 380 cases in the control group.

Statisticians suggest that we appropriately expand the sample size to reduce the impact of the central effect on the final results.

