### Statistical analysis

Multiple factors that affect this trial will be taken into consideration. Participates from different areas with similar school level will be stratified. A stratified randomizing method will also be adopted according to region, age, gender, etc. Similar stratified groups will be compared; the experimental and the control groups are launched within the same school.

We will use a linear mixed model to analyze incorporating repeated measures. Firstly, visual acuity is independent among subjects and is the primary indicator of observation. Otherwise, it will be measured at the end of each training session and followed up for 3 months. That is important to model the correlation of these repeated measurements.

Statistical analysis using SPSS 20.0 will be performed, and data management software will be used to construct the database. Dedicated staff will be assigned to oversee the management of electronic data, and a clinical research team will be deployed for data entry, validation, reporting, and answering questions. Normally distributed variables will be expressed as their mean and standard deviation (SD), and frequency (percentage) for categorical variables. Baseline characteristics between the intervention and control groups will be compared by performing a two-sample *t*-test and Wilcoxon rank-sum test for continuous variables with and without normal distribution, respectively. All *P*-values are 2-sided and considered statistically significant when less than 0.05.

Primary and secondary observation indexes will be analyzed by the superiority test depending on the treatment, using Per Protocol Set (PPS) and Full Analysis Set (FAS) datasets. The indices of safety evaluation will be analyzed using the Save Set (SS) dataset.

According to the ophthalmic disease efficacy evaluation standard in the Guidelines for Clinical Research of Traditional Chinese Medicine New Drugs:
Cure: visual acuity to normal (5.0)Significant effect: visual acuity improved by 4 lines or more with a visual chartImprovement: visual acuity improved by 2 lines or moreIneffective: visual acuity improved by less than 2 rows or decrease

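### The stated 380 + 190 at 2:1 gives about 81% power after 20% dropout, not 90%, partly because 2:1 puts most children in the arm with the smaller planning SD

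*Protocol article*

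**What the plan says.** Study design assigns 760 children to the experimental group and 380 to control, "groups in a 2:1 ratio". The abstract repeats the ratio.

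Sample size gives the planning values: "The treatment group was 4.98 ± 0.14" and "the control group was 4.92 ± 0.24". It sets a two-tailed alpha of 0.05, a "test efficacy of 0.9" and 20% dropout, and reports that "PASS 15.0 software calculation shows 380 in the experimental group and 190 in the control group". That total of 570 is doubled to 1140 because of a possible centre effect. No ICC or design effect is given. The ratio enters as an input, and the article gives no reason for it.

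Recruitment and Randomization place both arms within each school. Quality control adds that the arms have different teachers and separate classrooms. Table 1 and Second phase plan the meditation training for the control group in phase 2, depending on the phase 1 result, with the aim stated as "In order to ensure the maximum benefit of the subjects".

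**The concern.** Two things look wrong, and they are linked.

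- **The size does not match its inputs.** If 380 + 190 does not give 90% power after 20% dropout, the doubling starts from too small a base. Less of it is then left to absorb the centre effect it is meant for.
- **The ratio runs against the SDs.** The control mean is the imprecise one (SD 0.24 against 0.14), yet control gets half as many children. At a fixed total this lowers the precision of the primary comparison, and the article names no benefit in exchange.

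At stake are the credibility of the stated 90% power and precision that could be recovered without enrolling more children.

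**Working it through.** **Inputs** (Sample size, Study design): difference 4.98 − 4.92 = 0.06; ± read as SD, so 0.14 experimental and 0.24 control; two-sided alpha 0.05; power 0.90; dropout 20%; 2:1. Then (1.960 + 1.282)² = 10.507.

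**1. Trying to reproduce 380 + 190.** With k experimental children per control, n(control) = 10.507 × (0.24² + 0.14²/k) / 0.06².

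- k = 2: 10.507 × (0.0576 + 0.0098) / 0.0036 = 196.7, so 197 control and 394 experimental evaluable. Dividing the unrounded figures by 0.8 gives 246 + 492 = **738**, not 570.
- k = 1: 10.507 × 0.0772 / 0.0036 = 225.3 per arm. Divided by 0.8, this gives 282 + 282 = **564**.

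Welch-t versions are close: 498 + 249 at 2:1 and 284 + 284 = 568 at 1:1. Only variants that leave the stated inputs come within 3% of 380 + 190: a common SD of 0.19 with dropout applied as ×1.2 (382 + 191), or a one-sided alpha with ×1.2 (385 + 193).

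**2. Power of the stated size.** Variance = 0.14²/n(exp) + 0.24²/n(ctrl); power = Φ(0.06/SE − 1.960).

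| Evaluable children | Variance | Power (normal) | Power (Welch t) |
|---|---|---|---|
| 380 + 190, no dropout | 0.000355 | 89.0% | 88.8% |
| 304 + 152, after 20% dropout | 0.000443 | 81.3% | 80.9% |
| 228 + 228, same 570 at 1:1, after dropout | 0.000339 | 90.3% | 90.2% |

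**3. Cost of the ratio at equal total N.** Variance × N is 1.5 × 0.0196 + 3 × 0.0576 = 0.2022 at 2:1 and 2 × (0.0196 + 0.0576) = 0.1544 at 1:1. The ratio is 0.2022/0.1544 = **1.31**, so 1140 children at 2:1 carry the information of 1140/1.31 ≈ 871 at 1:1. The most efficient experimental share is 0.14/(0.14 + 0.24) = 37%, against 67% planned. With equal SDs the ratio would be (1.5 + 3)/4 = 1.125. 2:1 beats 1:1 only if the control SD is below √0.5 = 0.71 times the experimental SD; the plan has 0.24/0.14 = 1.71.

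**4. The enrolled 1140 after 20% dropout.** The centre-effect inflation is an assumption, applied here in proportion to each arm's variance.

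| Inflation | 2:1 (608 + 304) | 1:1 (456 + 456) |
|---|---|---|
| 1.0 | 98.1% | 99.6% |
| 1.5 | 90.8% | 96.5% |
| 2.0 | 81.3% | 90.3% |
| 2.5 | 72.2% | 83.1% |
| 3.0 | 64.3% | 75.9% |

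90% power holds up to an inflation of 1.55 at 2:1 and 2.02 at 1:1.

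**5. If clustering sits in classrooms.** Assume one classroom per arm in each of 27 schools and a common ICC ρ. Each arm's variance is then SD²/n × (1 + (n/27 − 1)ρ). The ρ that doubles the 2:1 variance is 0.084. Power is then 81.3% at 2:1 and 85.5% at 1:1, and the variance ratio falls to 0.000443/0.000395 = 1.12. In this model, 1:1 reaches 90% while 2:1 misses it only for ρ of about 0.046 to 0.064.

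**The case against.** A reader might infer that the trial as enrolled misses 90% power because of 2:1 and that 1:1 would rescue it. The article does not support that. The 81% against 90% contrast belongs to the base of 570. It carries over to 1140 only if the centre effect consumes the whole doubling, and it splits the two designs only for a proportional inflation of about 1.55 to 2.02. Both arms run within each school, so an additive school effect should largely cancel from the arm difference, leaving power near 98% against 99.6%. If clustering comes from separate classrooms, it depends mainly on the number of classrooms, which reallocating children does not change. The gain then shrinks, and 1:1 can miss as well.

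The other objections are also fair:

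- The shortfall at 570 is in part a calculation error, since a correctly sized 2:1 trial also reaches 90%.
- The SDs come from an early study that is not shown, and the planned repeated-measures mixed model could change both absolute power and the SD ratio.
- Unequal allocation can be a legitimate choice, its reason may stand in the full protocol, and control access in phase 2 is delayed and conditional.

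What stands is that the article prints a size its own inputs do not give, and that on those inputs the ratio costs precision. The usual access argument is weakened, though not removed, by the training planned for controls. If phase 2 opens, the number of meditation courses is 1140 under either ratio (760 + 380 or 570 + 570).

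**Conclusion.** The point holds in this limited form. The stated 380 + 190 delivers about 89% power before dropout and 81% after it, so Sample size does not support its 90% figure; 2:1 needs 738 before doubling. On the planning SDs, 2:1 inflates the variance of the arm difference by 31% relative to 1:1 at the same total (12.5% with equal SDs), and 1:1 needs 564, within the 570.

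The consequence for the enrolled 1140 is uncertain. Power at 2:1 runs from 98% with no centre effect to 81% if a proportional one absorbs the doubling, and lower if inflation exceeds 2. The gain from 1:1 is smaller where classroom clustering dominates. The absolute figures assume a simple two-group comparison, ± as SD, and evaluable numbers reduced by 20% in both arms. This is an avoidable loss of efficiency and a misstated power; it does not invalidate the design.

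**What to change.** 1. In Sample size, restate the power from the arm-specific SDs with 20% dropout, and show it over a stated range of centre-effect inflation, such as the 1 to 3 tabulated above, in place of an unexplained doubling.
2. If enrolment has not begun, change the allocation to 1:1 (570 + 570), total kept at 1140, in the abstract, Study design and Sample size. Trial status dates the first enrolment to December 2021 but also calls recruitment ongoing, so this must be checked first.
3. If 2:1 is kept, state the reason for it and the power it actually delivers.

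The restatement costs only wording. The change to 1:1 needs no extra children, but it requires a new random list and an ethics and registry amendment. It also moves 760 − 570 = 190 children out of the phase 1 training arm. That means fewer phase 1 safety records on the training, later access for those children, and 190 more controls to train if phase 2 opens.

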**Fig. 1 Fig1:**
[figure not shown]
Study design

**Table 1 Tab1:** General procedure and monitoring process

		Study period														
		Enrollment	Allocation	Intervention (phase 1)				Follow-up			Intervention (phase 2)				Termination	Unscheduled visit
Time point		–7~0 d^*****^	0 d	1st d^*****^	2~7d	8th d^*****^	9~30d	M1^*^	M2	M3	1st d	2~7d	8th d	9~30d		
***Enrollment***																
Screening visit		×														
Informed consent		×														
Inclusion and exclusion criteria		×														
History of myopia Intervention		×														
Diet habits		×	×													
Daily activity time distribution		×	×													
CISS^†^		×	×					×	×	×					×	×
Diagnosis		×						×	×	×						
Randomization			×													
Subject files		×						×	×	×						
Adverse events				×	×	×	×	×	×	×	×	×	×	×	×	×
Quit in advance				×	×	×	×				×	×	×	×	×	
Unscheduled visits								×	×	×						×
Allocation			×													
***Interventions***																
Meditation group (phase 1)	The first set of audio and video (1 h)			×		×										
	The second set of audio and video (15–20 min)				×		×									
Control group (phase 1)	Chinese eye exercises			×	×	×	×									
Control group (phase 2)	The first set of audio and video (1 h)										×		×			
	The second set of audio and video (15–20 min)											×		×		
***Assessment***																
Previous visual acuity		×	×													
Current visual acuity		×	×	×	×	×	×	×	×	×	×	×	×	×	×	×
Diopter and astigmatism		×	×				×	×	×	×				×	×	×

**d* day, *M* month, *1*^*st*^
*d* the first day, *8*^*th*^
*d* the eight day. †*CISS* Convergence Insufficiency Symptoms Survey

### Recruitment

In this trial, 1140 primary and secondary school students with simple myopia will be recruited from 27 schools in Sichuan and Hunan provinces or other cities with relatively uniform schooling conditions. School factors will be taken into consideration. We will choose participates from different areas with similar teaching level as the subjects. In the meanwhile, a comparison of the experimental group and the control group is launched within the same school in order to reduce the variance.

The main points for the diagnosis of simple myopia in China’s “Myopia Prevention and Treatment Guidelines” [19] will be used as a reference standard for recruitment: near visual acuity is normal; distance visual acuity is less than 1.0 (5.0 by the mucosal method); there are no pathological changes in the fundus; the progression is slow; vision can be corrected to normal with appropriate lenses, while other visual function indicators are mostly normal; and the subject recruited meet the quantitative criteria for myopia according to the “White Paper on Myopia Prevention and Control” of the International Myopia Institute (IMI) [20]: myopia diopter ≤ −0.50D.

